### 8.3 fMRI Analysis

The neuroimaging data will be analyzed using statistical parametric mapping 8 (SPM 8) (Wellcome Department of Cognitive Neurology London, UK; <http://www.fil.ion.ucl.ac.uk>). Preprocessing will include realignment, coregistration, spatial normalization into a standard space and smoothing. We will use traditional General Linear Model (GLM) voxel-wise analyses that will allow for the identification of threat-related brain activity. Baseline victimization scores as measured by the IVM (integrale veiligheidsmonitor) will be entered as regressors. Moreover, the effects of the training will be evaluated via 2 (Group: intervention, control) × 2 (Time: pre-, post intervention) interaction tests. Furthermore, we will study intrinsic connectivity during a resting state fMRI scan as a measure of brain system integrity. We will use region-of-interest (ROI) analyses for the amygdala to test our a priori hypotheses. The statistical thresholds we will employ are  $p < .05$  (smallvolume corrected) for ROI analyses and  $p < .001$  for whole-brain analyses.

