#### **4.1 Sample size calculation**

Sample size was calculated using the computerprogram SPSS Sample Power. In order to find a medium effect size (0.50) with two-sided  $\alpha=0.05$ , power=0.80 and taking 25% drop-out into account, 60 participants per group are needed. This means a total sample size of 120 participants.

Sample size in fMRI studies is usually not determined by power analyses, but by experiences with similar protocols. Exact power calculations are difficult because of the complex 'mass univariate' nature of brain imaging data as well as the difficulty to estimate effect sizes in different regions of interest beforehand. Previous studies suggest that in general, 20 participants are necessary per group to achieve sufficient power and acceptable reliability (Monti, 2011; Thirion et al., 2007). Therefore, in the fMRI-part of the proposed study, 22 participants will be included per group.

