## 6.2 Randomisation, blinding and treatment allocation

Participants will be allocated to either the treatment group or control group at random by means of randomisation on the factors: site, gender and participation in fMRI substudy. We will correct for randomisation factors in the analysis, in order to prevent bias. At all sites experienced interviewers are available that will be blinded to the study condition. Interviewers remain blind to the treatment allocation, but patients cannot be blinded after care allotment.

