| Positive and negative symptoms *(PANSS)                 |                      | x                |                       | x                      | x                  | x                   | x                    |
| Brief negative symptom scale * (BNSS)                   |                      | x                |                       | x                      | x                  | x                   | x                    |
| MiniSCAN                                                |                      | x                |                       |                        |                    |                     |                      |
| Integrale veiligheidsmonitor (IVM)                      |                      |                  | x                     | x                      | x                  | x                   | x                    |
| Revised Conflict Tactics Scale (CTS2)                   |                      |                  | x                     | x                      | x                  | x                   | x                    |
| Self-expression and control (ZECV)                      |                      |                  | x                     | x                      | x                  |                     |                      |
| Internalized stigma of mental illness (ISMI)            |                      |                  | x                     | x                      | x                  |                     |                      |
| Self-esteem rating scale – short form (SERS-SF)         |                      |                  | x                     | x                      | x                  |                     |                      |
| Screening Risico Verslavingsproblemen (Substance abuse) |                      |                  | x                     | x                      | x                  | x                   | x                    |

|                                                     |  |   |   |   |   |   |   |
|-----------------------------------------------------|--|---|---|---|---|---|---|
| Schaal Interpersoonlijk Gedrag (SIG)                |  |   | x | x | x |   |   |
| Faux pas task                                       |  |   | x | x | x |   |   |
| Wall of faces task**                                |  |   | x | x |   |   |   |
| Emotional faces paradigm**                          |  |   | x | x |   |   |   |

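### The fMRI training effect is tested as a Group x Time interaction, which is a change-score test; adjusting for the pre-training scan would be more efficient at almost no cost

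*Protocol*

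**What the plan says.** Section 8.3 (fMRI Analysis) fixes the test of the training effect: "the effects of the training will be evaluated via 2 (Group: intervention, control") crossed with two time points, "Time: pre-, post intervention) interaction tests". The instrument schedule in section 6.3 (Table 5) places both fMRI tasks, the Wall of faces task and the "Emotional faces paradigm", at the pre- and post-assessment only. Each scanned participant therefore has one baseline and one post-training value per contrast.

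The only baseline regressor that 8.3 names is the victimization score: "Baseline victimization scores as measured by the IVM (integrale veiligheidsmonitor) will be entered as regressors". Section 6.2 makes participation in the fMRI substudy a randomisation factor, alongside site and gender, and adds: "We will correct for randomisation factors in the analysis, in order to prevent bias". No section adjusts the post-training scan for the pre-training scan.

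On size, the sample size section says that "in the fMRI-part of the proposed study, 22 participants will be included per group", on this ground: "Sample size in fMRI studies is usually not determined by power analyses, but by experiences with similar protocols". For ROI analyses, 8.3 sets a small-volume-corrected threshold of 0.05; for whole-brain analyses it sets 0.001.

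**The concern.** With two time points, the interaction subtracts the whole baseline value from the post-training value, however weakly the two scans correlate. If the correlation is modest, the subtraction brings in baseline noise. Estimating the baseline slope instead of fixing it at 1 removes that excess. Because participants are randomised within the fMRI stratum, the adjusted comparison is as valid as the planned one.

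What is at stake is the chance of detecting a real effect of training on brain response. The fMRI part has 44 of the trial's 120 participants, and its size was set by convention and not by a power calculation, so it has little margin to lose efficiency. The baseline scans needed for the adjustment are already planned.

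**Working it through.** **Inputs from the protocol.** One pre and one post scan (6.3, Table 5); 22 per group (sample size section); two-sided 0.05. The fMRI sample size has no power calculation behind it, so there is no stated figure to reproduce.

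**Assumed inputs.** The protocol gives no pre-post correlation rho and no fMRI effect size. I vary rho and take d = 0.50, borrowed from the main trial's sample size, and d = 0.80. Effects are in units of the post-scan SD, with equal SDs before and after.

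**Step 1: the interaction is a change-score test.** On simulated data with 22 per group, the 2 x 2 mixed-model interaction F was 2.1781. The squared two-sample t on post-minus-pre change was also 2.1781.

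**Step 2: variances.** In units of SD²:
- change score: 2(1 − rho)
- adjusted for the pre scan: 1 − rho² = (1 − rho)(1 + rho)
- ratio, change to adjusted: 2/(1 + rho)

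The ratio is 2/1.3 = 1.54 at rho 0.3, 2/1.5 = 1.33 at 0.5, 2/1.7 = 1.18 at 0.7 and 2/1.9 = 1.05 at 0.9.

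**Step 3: power.** Noncentral t with noncentrality (d/s) × √(22/2), where s is the square root of the variance above. Degrees of freedom are 2 × 22 − 2 = 42 for change and 41 for the adjusted comparison. For example, at d = 0.50 and rho 0.5 the change score has s = 1 and noncentrality 0.50 × √11 = 1.66. The adjusted comparison has s = √0.75 = 0.866 and noncentrality 1.91.

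| rho | d = 0.50: change | d = 0.50: adjusted | d = 0.80: change | d = 0.80: adjusted |
|---|---|---|---|---|
| 0.3 | 28% | 40% | 59% | 78% |
| 0.5 | 37% | 46% | 74% | 85% |
| 0.7 | 55% | 62% | 92% | 95% |
| 0.8 | 73% | 77% | 98% | 99% |
| 0.9 | 95% | 96% | >99% | >99% |

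Comparing post scans alone gives 37% at d = 0.50. The change score matches that at rho 0.5 and falls below it at lower rho.

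**Step 4: equivalent sample size.** To match the adjusted comparison with 22 per group, the change score needs about 22 × 2/(1 + rho) per group: 33.8 at rho 0.3, 29.3 at 0.5 and 25.9 at 0.7.

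**Step 5: how robust is the gain?**
- *Site and gender.* If all seven institutions contribute, these use 6 + 1 = 7 further degrees of freedom, leaving 41 − 7 = 34. At d = 0.50 and rho 0.5 the adjusted power stays at 46%; the loss from the degrees of freedom is under 1 point.
- *Stricter threshold.* The table treats the ROI as one mean value tested at an uncorrected 0.05. If the small-volume correction acted like a threshold of 0.005 (an assumption), power at rho 0.5 would be 11% against 16% at d = 0.50, and 39% against 54% at d = 0.80. Both methods lose power, and the adjusted one stays ahead.

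**The case against.** The strongest reply is that nothing in 8.3 is invalid. Under randomisation the interaction test is unbiased and keeps its type I error, and it is a common choice for pre-post imaging. That stands: the point concerns efficiency only.

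The second reply is that 22 per group is the only substudy figure in the calculation. That also stands. At rho 0.7 the gain is about 7 points for d = 0.50 and about 3 or 4 for d = 0.80, and above that it is small. A reader might infer that subtracting the baseline is worse than ignoring it. That needs rho below 0.5, and the protocol gives no value of rho.

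Third, the power table does not describe the planned test, which is voxel-wise and small-volume corrected. A reader might take 37% against 46% as the substudy's actual power. The documents do not support that; the figures show only the relative standing of two methods for a single ROI value.

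Fourth, a reader might infer that the training effect in the amygdala is the study's a priori fMRI hypothesis, or that the victimization score was meant to stand in for the baseline scan. Section 8.3 supports neither. It reserves the amygdala ROI for a priori hypotheses without saying which. Its sentence on the victimization regressor comes before the one on training effects and can be read as a separate association analysis.

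Fifth, averaging over an ROI is itself a change from a voxel-wise test and can dilute a focal effect. That is a real, if small, downside of the simplest implementation. It does not count against baseline adjustment as such.

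**Conclusion.** The point holds as a modest efficiency improvement. The planned interaction is a change-score test, and no section adjusts the post-training scan for the pre-training scan. With equal SDs, the planned test has 2/(1 + rho) times the variance of the adjusted comparison. In the single-ROI illustration at d = 0.50, that costs about 12 power points at rho 0.3, 10 at 0.5, 7 at 0.7 and under 5 from 0.8 upwards. Both d and rho are assumptions, and absolute power under the small-volume correction would be lower for both methods.

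Not knowing rho is no reason to keep the change score as the main ROI test: apart from one degree of freedom, the adjusted comparison is at least as precise at any rho. The consequence is limited. Section 6.1.2 lists the fMRI tasks among the mediating factors, for substudy participants only, and the primary victimization outcome, measured by the IVM and CTS2, is not affected.

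**What to change.** In 8.3, for the amygdala ROI test of the training effect, model the post-training contrast on group, with the pre-training value of the same contrast as a covariate. Add the randomisation factors that 6.2 already commits to and that vary within the substudy, namely site and gender. The simplest implementation extracts the mean ROI contrast per participant and scan from the first-level images. State its downside, possible dilution of a focal effect, and keep the planned small-volume-corrected 2 x 2 interaction and the whole-brain map as supporting analyses.

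The cost is a short revision of 8.3, an ROI extraction and one degree of freedom for the baseline term. The degrees of freedom for site and gender are already implied by 6.2. No extra scans are needed.

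### The whole-brain fMRI threshold is fixed at p<.001 with no named multiplicity control; read as uncorrected, a false-positive cluster is very likely in any null contrast

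*Protocol*

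**What the plan says.** Section 8.3 of the protocol gives both fMRI significance thresholds in one sentence. The ROI threshold is p<.05 and is marked as corrected; the whole-brain threshold is p<.001 with no qualifier: "smallvolume corrected) for ROI analyses and $p < .001$ for whole-brain analyses". The whole-brain threshold is called neither corrected nor uncorrected, and no FWE, FDR or cluster-extent criterion goes with it.

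The same section describes the whole-brain tests as "General Linear Model (GLM) voxel-wise analyses that will allow for the identification of threat-related brain activity". It evaluates the training through "2 (Group: intervention, control) × 2 (Time: pre-, post intervention) interaction tests" and enters baseline victimization scores as regressors. The a priori hypotheses are assigned to one region: "We will use region-of-interest (ROI) analyses for the amygdala to test our a priori hypotheses".

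Preprocessing includes "spatial normalization into a standard space and smoothing", with no kernel size. No search volume is given.

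The sample-size section (the second section numbered 4.1) sets the substudy size, "in the fMRI-part of the proposed study, 22 participants will be included per group". It also refers to the "complex 'mass univariate' nature of brain imaging data", but only to explain why no exact power calculation was done.

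**The concern.** A per-test level of .001 looks strict, but a whole-brain map consists of a very large number of correlated tests. Over independent tests, p<.001 keeps the family-wise rate near 5% for only about 50 of them, and a smoothed brain volume contains far more independent units than that. Because the sentence labels one threshold as corrected and leaves the other bare, an analyst following it could accept any supra-threshold cluster as significant.

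Cerebral effects are part of the stated objective (section 2), and both fMRI tasks appear among the mediating factors in Table 4 (section 6.1.2). The amygdala is the only ROI named, so findings elsewhere would rest on the whole-brain threshold. A chance cluster in the Group by Time map could then be reported as a cerebral effect of the training, or as support for its proposed mechanism.

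**Working it through.** The protocol states no family-wise rate, so there is no figure to reproduce. The check works out what p<.001 implies if it is the whole decision rule.

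**Inputs from the protocol**
- Whole-brain threshold p<.001, voxel-wise general linear model (8.3).
- 22 per group (second section numbered 4.1). The Group by Time interaction is a two-sample t test on change, so df = 22 + 22 − 2 = 42 if everyone completes.

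**Assumptions, not in the protocol**
- Search volume V of 1.2 to 1.5 litres, treated as a sphere of radius r.
- Effective smoothness F (FWHM) of 8 to 25 mm.
- No extent rule, one direction of effect, contrast null throughout the brain.

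**Step 1: independent tests.** The family-wise rate is 1 − (1 − .001)^m. For m = 50 it is 4.9%, for m = 500 it is 39%, for m = 1000 it is 63%, and for m = 2995 it is 95%. The number of resolution elements, V/F³, is 694 to 868 at 12 mm and 150 to 188 at 20 mm, well above 50 in both cases.

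**Step 2: random field theory for a t field.** With df = 42, one-sided p = .001 gives t = 3.30. The expected number of false clusters is approximated by the expected Euler characteristic:

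E = ρ0 + (4r/F)·ρ1 + (2πr²/F²)·ρ2 + (V/F³)·ρ3

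The t-field densities at t = 3.30 are ρ0 = .0010, ρ1 = .0024, ρ2 = .0052 and ρ3 = .0101. The chance of at least one false cluster is P = 1 − exp(−E).

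Worked case, V = 1.2 litres and F = 12 mm (r = 65.9 mm): E = .001 + 21.97 × .00237 + 189.6 × .00516 + 694.4 × .01006 = .001 + .052 + .979 + 6.983 = 8.02, so P = 1 − exp(−8.02) = .9997.

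| FWHM | E (1.2 to 1.5 L) | P(at least one false cluster) |
|---|---|---|
| 8 mm | 25.9 to 32.1 | >.999 |
| 10 mm | 13.5 to 16.8 | >.999 |
| 12 mm | 8.0 to 9.9 | >.999 |
| 15 mm | 4.2 to 5.2 | .986 to .995 |
| 20 mm | 1.9 to 2.3 | .85 to .90 |
| 25 mm | 1.0 to 1.3 | .64 to .71 |

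With dropout to df 38 or 30 the probabilities rise slightly (at 20 mm and 1.2 L: .854 and .868, against .849).

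**Step 3: simulation.** Null smooth fields were generated for 22 against 22, with 1.2 litres, 4 mm voxels and 40 runs per setting. At least one false cluster appeared in 40/40 runs at 10 mm, 40/40 at 12 mm, 36/40 at 15 mm and 31/40 at 20 mm. Mean cluster counts were 7.6, 5.1, 2.4 and 1.6. These are below the formula, and at 20 mm the proportion is 78% against 85%. A coarse grid that misses small peaks is a likely reason, and 40 runs is few. The conclusion is the same.

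**Step 4: an arbitrary extent rule.** In the same simulation, requiring a cluster of at least 270 mm³ (ten 3 mm voxels) still left a false cluster in 60 to 73% of runs. A small fixed extent would therefore not be enough.

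**Step 5: what 5% would need.** A voxel-level FWE rate of .05 (df 42, 1.2 to 1.5 L) needs t of about 5.8 to 5.9 at 8 mm, 5.4 to 5.5 at 12 mm, 5.2 at 15 mm and 4.8 to 4.9 at 20 mm. At 8 to 20 mm that is a per-voxel p of roughly 3×10⁻⁷ to 9×10⁻⁶, against .001.

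**The case against.** The strongest defence is that the text is silent. It does not say uncorrected, and p<.001 could be meant as a cluster-forming height with cluster-level correction on top, which would remove the problem. An analysis plan that is not at hand might say so, and detail of that kind is often left to it. The silence is real, so an absence of correction is an inference and not a stated choice. But the sentence presents itself as the list of thresholds to be used and specifies the correction for one of the two. If cluster-level inference was intended, the criterion that decides significance is missing from that list, and the same edit is needed.

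The second defence is limited reach, and it stands. The a priori amygdala hypotheses use small-volume correction, the fMRI part is a substudy of 22 per group within a trial of 120, and the victimization outcome is analysed separately (8.2).

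A reader might also infer more than the protocol supports:
- That false clusters are almost certain in every contrast. The calculation applies only to contrasts that are null throughout the brain; task activation maps are not expected to be. It also depends on smoothness, volume and the absence of an extent rule, none of which the protocol gives. At 20 to 25 mm the probability is 64 to 90%, not near certainty.
- That the resting-state analysis is tested at this threshold. Section 8.3 says only that intrinsic connectivity will be studied, not that it will be a whole-brain voxel-wise test at p<.001.

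**Conclusion.** The concern holds in this form: section 8.3 fixes a whole-brain threshold with no named error control, next to an ROI threshold that has one. The natural reading is uncorrected. On that reading the family-wise error per null contrast is about 85% to above 99.9% at 8 to 20 mm FWHM and about 64 to 71% at 25 mm, by random field theory with df 42. Every value is more than ten times 5%. The simulation gives somewhat lower figures at 15 and 20 mm (90% and 78%) and the same conclusion.

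These sizes rest on an assumed volume and smoothness, no extent rule and one direction of effect. What is at risk is the credibility of whole-brain findings outside the amygdala, above all a Group by Time cluster read as an effect of the training. It is worth correcting, but it does not threaten the trial's main conclusion.

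**What to change.** Amend the threshold sentence in section 8.3 along these lines: whole-brain maps are formed at voxel-wise p<.001, and a whole-brain effect is claimed only if it reaches FWE-corrected p<.05 at cluster level (or peak level, chosen in advance); maps shown without that correction are exploratory. The amygdala ROI rule can stay as it is.

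If cluster-level correction was already intended, the amendment only writes it down. It needs no new data and no change in design or sample size. The price is some whole-brain sensitivity. Peak-level control is the costlier option: the required t rises from 3.30 to about 5.2 at 15 mm smoothness. Cluster-level control keeps p<.001 as the height and sets the nominal rate at 5% per contrast.

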## ETHICAL CONSIDERATIONS

### **8.4 Regulation statement**

The study will be conducted according to the principles of the Declaration of Helsinki (version 10, October 19th 2013) and in accordance with the Medical Research Involving Human Subjects Act (WMO) and other guidelines, regulations and Acts (Wet Geneeskundige Behandelingsovereenkomst, Wet Bescherming Persoonsgegevens, Wet Beroepen Individuele Gezondheidszorg, Kwaliteitswet Zorginstellingen, Privacyreglement van de zorginstelling).

### **8.5 Recruitment and consent**

Chapter 2 shows a flow chart of the study design and main procedures. First the onsite therapist will answer seven screening questions about their patients (see appendix F1). When the answers are in accordance with the selection criteria (see 3.2 and 3.3 for inclusion and exclusion criteria) the patient will receive a phone call from his/her psychomotor therapist or another caregiver from his/her mental health institution. The assessor will inform the patients about the study and ask them if they are interested in participation and if they would like to receive an information letter about the study (see appendix E2). The assessor will send this letter by mail or email depending on what the patient prefers. Patients have two weeks to consider their participation. After two weeks, patients are contacted again to ask whether they decided to participate in the study.

During the first phone call all patients are also invited for a one hour information meeting. In this meeting patients will get more detailed information about the study procedures and the intervention and get acquainted with the trainers. The patients are invited to bring family and/or friends to this meeting in order to support and motivate patients for participation. Also, their questions about the intervention can be answered. All the involved mental health care professionals will also receive an invitation for the meeting (see appendix E3). When patients have second thoughts after the meeting they are free to refrain. After the information meeting the assessor will call all the interested patients to make an appointment for the selection assessment. The assessor will tell them again about the study procedures, randomization and intervention in case something was not clear during the meeting or someone did not attend the meeting. In addition, the patients are told that the intervention is in an experimental phase, and that no guarantees can be given regarding decreasing victimization risk. The selection assessment will start two to six weeks after the information meeting. On the day of the assessment the assessor first asks the patients to read and sign an informed consent form (see appendix E1).

